#### Histological and Histomorphometric Analysis

Histological and histomorphometric analysis will be performed for at least 3 patients who received dental implants after alveolar cleft reconstruction, in accordance with previously published procedures [32]. Briefly, the implant preparation site will be developed using a trephine burr (⌀ 2.0 mm × 10.0 mm in length) that allows biopsy specimen collection from the implant site without interfering with the regular procedure. The biopsy specimens will be fixed in ﻿4% phosphate-buffered formaldehyde, dehydrated in an ascending series of ethanol, and embedded in 80% methylmethacrylate (BDH Chemicals) supplemented with 20% dibuthylphtalate (Merck), 8 g/L lucidol CH-50 L (Akzo Nobel), and 22 μL/10 mL N,N-dimethyl-p-toluidine (Merck). The biopsy specimens will be cut into ﻿5-μm-thick sections and subjected to 2 different staining procedures (﻿Goldner’s trichrome and Tartrate-resistant acid phosphatase staining). Several histomorphometric parameters (bone volume, osteoid volume, graft volume, and number of osteoclasts) will also be measured for quantitative analysis [32]. Two trained examiners will perform the histologic and histomorphometric analyses. In case of dispute, the biopsies will be reanalyzed to reach consensus.

### Statistical Analysis

Since this is a single-arm safety study, statistical analyses will not be performed.

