### Sample Size

This is a first-in-human phase I clinical trial aimed to obtain insight on the safety and feasibility of the treatment with the BCP-MFAT combination. We assume that no SAEs or AEs will occur, based on our clinical experience with other applications of MFAT and the well-proven safety of BCP. Upon consultation with a statistician, a sample size of 8 individuals is expected to be sufficient for this trial.

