### Randomization and Blinding

Since this trial comprises only 1 type of treatment, no randomization or blinding to the treatment is possible.

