### Evaluation Methods

#### Safety Assessment Based on Physical Examination and Laboratory Measurements

When an SAE occurs, it will be concluded that a combination of MFAT and BCP is not yet safe in the current setting. For AEs, if they do not occur at a higher frequency than that in patients treated with standard care (autologous bone) or can be resolved through noninvasive conventional methods (eg, analgesics or antibiotics), the combination of MFAT and BCP will be considered safe. In all other cases, combination of MFAT and BCP will not be considered safe yet.

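### The plan fixes a categorical safe verdict from 8 patients and excludes statistical analysis, so the report would not show that 0/8 SAEs leaves risks up to 36.9% open

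*Protocol article*

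**What the plan says.** Four sections of the protocol article bear on this point.

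- **Safety Assessment Based on Physical Examination and Laboratory Measurements** (repeated in the abstract's Conclusions) sets the decision rule. For SAEs: "When an SAE occurs, it will be concluded that a combination of MFAT and BCP is not yet safe in the current setting". For AEs there are two alternative routes to a favourable verdict. One is frequency: "if they do not occur at a higher frequency than that in patients treated with standard care (autologous bone". The other is that the AEs resolve by noninvasive conventional means. If either route is met, "the combination of MFAT and BCP will be considered safe".
- **Sample Size** describes a first-in-human phase I trial that seeks insight into safety and feasibility. It states: "We assume that no SAEs or AEs will occur, based on our clinical experience with other applications of MFAT" (the proven safety of the ceramic is also cited). After advice from a statistician, "a sample size of 8 individuals is expected to be sufficient for this trial".
- **Statistical Analysis** is one sentence: "Since this is a single-arm safety study, statistical analyses will not be performed".
- **Discussion**, last paragraph, says that the main conclusions will rest on the safety parameters, in particular on whether AEs or SAEs occur.

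The article states no acceptable SAE rate, no standard-care AE rate and no confidence level.

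**The concern.** The primary output of this trial is a verdict on safety. The protocol fixes the wording of that verdict and, separately, excludes the analysis that would show how much 8 patients can support.

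The exclusion is justified by the single-arm design. That design prevents a randomised comparison between arms. It does not prevent the number of patients with an event from being given as a proportion with an exact interval, which needs only one arm. The exclusion also sits badly with the AE rule: deciding whether AEs are more frequent than under autologous bone is a comparison of frequencies, and the Statistical Analysis section leaves it with no method.

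At stake is the published conclusion. Followed as written, the report could call the combination safe on the strength of no SAE in 8 patients, with nothing beside that statement to show which risks the data leave open.

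**Working it through.** **Inputs**

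- Number of patients: n = 8 (Sample Size; Study Design).
- SAE criterion: one or more SAEs means not yet safe, so the criterion is passed only with 0/8 (Safety Assessment).
- Confidence level: not in the document. 95% is assumed.
- True SAE risks of 5%, 10%, 20% and 30%: illustrative assumptions. The document gives no acceptable rate.

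**The plan's own figure.** The size of 8 cannot be reproduced, because no rate, precision or confidence level accompanies it. The section makes no power or precision claim, so there is no stated calculation that could be wrong.

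**Step 1: what 0/8 excludes.** With no events in n patients, the exact (Clopper-Pearson) upper limit is

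- two-sided 95%: 1 − 0.025^(1/8) = 0.369, or 36.9%;
- one-sided 95%: 1 − 0.05^(1/8) = 0.312, or 31.2%.

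These are one result under two conventions, not the ends of a range.

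**Step 2: what 1/8 shows.** One patient in 8 is 12.5%. The exact two-sided 95% interval runs from 1 − 0.975^(1/8) = 0.003 to the p that solves (1−p)^8 + 8p(1−p)^7 = 0.025, which is p = 0.527. The interval is 0.3% to 52.7%. This bears on the AE rule: with one patient affected, a comparison with any outside AE frequency would rest on an estimate this wide.

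**Step 3: how often the SAE criterion is passed.** For a true SAE risk p per patient, the chance of no SAE in 8 is (1−p)^8.

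| True SAE risk (assumed) | Chance of no SAE in 8 | Chance of at least one |
|---|---|---|
| 5% | 0.95^8 = 66% | 34% |
| 10% | 0.90^8 = 43% | 57% |
| 20% | 0.80^8 = 17% | 83% |
| 30% | 0.70^8 = 6% | 94% |

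**Step 4: the sections side by side.** The Safety Assessment section asks whether a frequency is higher than a reference frequency. The Statistical Analysis section says no analysis will be performed, because there is one arm. The first cannot be carried out without at least an observed proportion and a statement of its uncertainty. The reason given in the second does not rule out either.

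**The case against.** The strongest defence is that this is an IDEAL stage 1, first-in-human study, for which 8 patients is not unusual. The Sample Size section speaks only of gaining insight. The SAE threshold is the strictest available, since one event is enough for an unfavourable verdict. Safety follow-up continues for 3 more years, with yearly safety reports to the ethics committee. No data are lost: with n = 8 and the counts reported, any reader can compute the interval. The Statistical Analysis sentence may be meant to exclude only inferential testing, as the Bergland grades and histomorphometric measures are still to be quantified.

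Much of this stands, and it limits the point. Several stronger readings are tempting, but the document does not support them:

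- *That 8 is the wrong sample size.* The section claims neither power nor precision. It places the statement "We assume that no SAEs or AEs will occur" and the number 8 near each other but does not say that the second was derived from the first.
- *That the zero-event assumption contradicts a list of expected complications.* The Recruitment section lists possible complications disclosed at consent, one of them marked as unlikely. Possible is not expected. Likewise, a rule for judging AEs if they occur is a contingency, not a contradiction.
- *That only event-free patients lead to a safe verdict.* The rule also admits AEs that are no more frequent than under standard care or that resolve noninvasively.
- *That an unacceptably risky graft would often pass.* That needs an acceptable SAE rate, which the document does not give. The miss probability is 43% at a true risk of 10% but only 6% at 30%.

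The defence does not rescue the conclusion itself. Gaining insight is a modest aim, but the Safety Assessment section goes beyond it to a categorical verdict. Nor can the gap be treated as a detail left to an unseen analysis plan: the protocol does not defer the analysis but declines it, so a later plan that added intervals would depart from this text.

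**Conclusion.** The point holds as one about the conclusion and its reporting. The protocol commits to a categorical safe verdict from 8 patients and excludes statistical analysis for a reason that does not follow from the single-arm design, while its own AE rule needs a comparison of frequencies. At the assumed 95% level, the most favourable SAE result, 0/8, excludes only risks above 36.9% (two-sided exact) or 31.2% (one-sided). A true SAE risk of 10% would pass the SAE criterion 43% of the time.

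The 95% level and the illustrative risks are assumptions. The calculation treats patients as independent with a common risk and assumes that all 8 are evaluated. A reader might infer that the trial is too small or its sample-size section wrong; neither follows. Eight patients can serve the stated aim if the report says what 8 patients can and cannot show.

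**What to change.** Three changes of wording:

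1. **Statistical Analysis.** State that no hypothesis tests will be done, but that the number and proportion of patients with at least one SAE, and with at least one AE, will be reported with exact (Clopper-Pearson) 95% confidence intervals.
2. **Sample Size.** Keep the stated assumption on record, since the trial is already in follow-up, and add the precision that 8 patients give: 0/8 excludes only SAE risks above about 37% (two-sided 95%).
3. **Safety Assessment and the abstract's Conclusions.** Qualify the favourable verdict as preliminary, for example: *the prespecified safety criteria were met in 8 patients; event risks up to the upper confidence limit are not excluded.* This wording stays true when the rule is met with AEs present. A phrase such as *no safety signal* would not.

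Intervals alone do not supply the standard-care AE frequency that the rule refers to. The report must state which reference rate was used, so that the AE interval can be read against it.

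Cost: no more patients, visits or data. The changes need a minor amendment, which under the Amendments section requires prior approval by the ethics committee and the competent authority. The stated conclusion becomes less favourable.

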## Results

The primary outcome parameter will be safety after 6 months’ follow-up, assessed by closely monitoring possible occurrences of AEs or SAEs, radiographic imaging, blood tests, and physical examinations. For efficacy, radiographic imaging will be used for clinical grading of the bone construct using the Bergland scale. In addition, bone parameters such as bone volume, osteoid volume, graft volume, and number of osteoclasts will be histomorphometrically quantified. We expect that the feasibility and safety of the procedure will be apparent, as well as its initial efficacy. Recruitment started in November 2019, and the trial is currently in the follow-up stage. This protocol’s current version is 1.0, dated September 15, 2019.

## Discussion

In recent years, there has been increasing interest in the use of adipose tissue for cleft lip and palate reconstruction [33]. Its applicability mostly relies on the quantity of the tissue, the ease of surgical harvesting, and the type of surgical reconstruction in which the tissue is used, for example, correction of cleft lip volume asymmetry [34,35], improvement of velopharyngeal insufficiency after cleft lip and palate repair [36,37], or as an extra flap in cleft palate repair [38-41]. In this study, we will make use of the BFP for bone reconstruction. The BFP is a specialized adipose tissue rich in vascular supply, which is easy to harvest via the oral cavity during an intraoral surgery with minimal morbidity and discomfort [42].

Until now, there are only few reports on the use of adipose tissue as a regenerative compound for bony cleft reconstruction—a phase I clinical trial conducted by Khojasteh et al [24] and an animal study using ASCs for alveolar cleft repair [43]. Both studies used collagenase digestion of the tissue and culture expansion to obtain ASCs for personalized cleft reconstructions. An alternative is the SVF derived from adipose tissue via collagenase digestion, which requires a shorter time frame and may yield similar stem cell–like quantities, allowing intraoperative applications [44,45]. A previous clinical study by Prins et al [44] showed that addition of SVF in an intraoperative setting to calcium phosphate ceramics had an additive value on bone formation, implying that SVF can provide osteoinductivity when combined with calcium phosphate. However, so far, regulatory issues and relative expensive SVF production procedures prohibit its wide applicability [22,23]. Mechanically processed fat or MFAT has emerged as a rapid processing alternative to SVF and is being considered minimally manipulated and thereby less regulation restricted [22,23].

This is the first in human study evaluating a combination of MFAT and biphasic BCP as a regenerative graft for alveolar cleft reconstruction [46,47]. BCP is a ceramic scaffold with a balanced ratio between the less-soluble HA and the more-soluble TCP that results in mechanical and biological properties to support bone and cartilage tissue production [48]. It is sufficient for bone reconstruction in non–load-bearing applications and already accepted as standard of care for certain maxillofacial reconstructions [49].

Recently, calcium phosphate has been applied for alveolar cleft surgeries as well [16,17]. Patients within that study were treated at ages of 9-10 years, which is within the optimum age range for SABG [1]. However, we did not want to enroll children in a safety study with this novel concept in clinical practice. Therefore, although we realize that surgeries at a later age will (1) not make optimal use of the growth spurt and (2) may result in cases having larger or even critical size defects (which will not heal unless supplemented with grafts), we chose to only include older adolescent and adult patients, who are themselves capable of being involved in decision-making. We will perform this study in Indonesia because unoperated patients in this age group are difficult to find in Europe.

This is primarily a safety study, so the main conclusions of the study will be based on safety parameters, particularly on the occurrence of AEs or SAEs.

## Appendix

Multimedia Appendix 1 SPIRIT (Standard Protocol Items: Recommendations for Interventional Trials) checklist.

## Abbreviations

AE: adverse event
ASC: adipose stem cell
BCP: biphasic calcium phosphate
BFP: buccal fat pad
HA: hydroxyapatite
IDEAL: innovation, development, exploration, assessment, and long-term study
MFAT: microfragmented fat
SABG: secondary alveolar bone grafting
SAE: severe adverse event
SVF: stromal vascular fraction
